## Abstract

**Background:**

Patients with type 2 diabetes (T2DM) have an increasing need for personalized and Precise management as medical technology advances. Artificial intelligence (AI) technologies on mobile devices are being developed gradually in a variety of healthcare fields. As an AI field, knowledge graph (KG) is being developed to extract and store structured knowledge from massive data sets. It has great prospects for T2DM medical information retrieval, clinical decision-making, and individual intelligent question and answering (QA), but has yet to be thoroughly researched in T2DM intervention. Therefore, we designed an artificial intelligence-based health education accurately linking system (AI-HEALS) to evaluate if the AI-HEALS-based intervention could help patients with T2DM improve their self-management abilities and blood glucose control in primary healthcare.

**Methods:**

This is a nested mixed-method study that includes a community-based cluster-randomized control trial and personal in-depth interviews. Individuals with T2DM between the ages of 18 and 75 will be recruited from 40-45 community health centers in Beijing, China. Participants will either receive standard diabetes primary care (SDPC) (control, 3 months) or SDPC plus AI-HEALS online health education program (intervention, 3 months). The AI-HEALS runs in the WeChat service platform, which includes a KBQA, a system of physiological indicators and lifestyle recording and monitoring, medication and blood glucose monitoring reminders, and automated, personalized message sending. Data on sociodemography, medical examination, blood glucose, and self-management behavior will be collected at baseline, as well as 1,3,6,12, and 18 months later. The primary outcome is to reduce HbA1c levels. Secondary outcomes include changes in self-management behavior, social cognition, psychology, T2DM skills, and health literacy. Furthermore, the cost-effectiveness of the AI-HEALS-based intervention will be evaluated.

**Discussion:**

KBQA system is an innovative and cost-effective technology for health education and promotion for T2DM patients, but it is not yet widely used in the T2DM interventions. This trial will provide evidence on the efficacy of AI and mHealth-based personalized interventions in primary care for improving T2DM outcomes and self-management behaviors.

**Trial registration:**

Biomedical Ethics Committee of Peking University: IRB00001052-22,058, 2022/06/06; Clinical Trials: ChiCTR2300068952, 02/03/2023.

**Supplementary Information:**

The online version contains supplementary material available at 10.1186/s12889-023-16066-z.

## Background

Diabetes mellitus is a common chronic disease with a high prevalence and mortality rate. The number of people with diabetes aged 20–79 years is estimated to be at 537 million in 2021, which is still rising and is expected to reach to 643 million by 2030, and 783 million by 2045. There are 140.9 million adults with diabetes in China, with a prevalence of 11.9%, causing a great health and economic burden [1]. However, diabetes control and treatment in China is inadequate, indicating the need for effective and innovative methods to improve diabetes prevention and treatment.

Diabetes self-management is one of the cornerstones of diabetes control, and it entails lifestyle changes such as diet and physical activity (PA), blood glucose monitoring, and medication administration on a regular basis. The body of evidence has shown the benefits of diabetes self-management on metabolic control, outcome improvements and reduced risk of all-cause mortality, which is recommended by international consensus [2]. Dietary management involves healthy dietary patterns to achieve and maintain optimal blood glucose, lipid, and blood pressure levels [3–6], such as Mediterranean diet [7, 8], the Dietary Approaches to Stop Hypertension (DASH) diet [9–11], the low calorie energy deficit diet [12–14], the low carbohydrate diet [15–17], vegan and vegetarian diets [18, 19], intermittent fasting and macrobiotic diets [20], and the low glycaemic index or glycaemic load dietary patterns [21–24]. In addition, a sedentary lifestyle, which parallels the global obesity epidemic, is also a crucial risk factor of T2DM [25, 26]. Physical activity, such as various leisure time PA and occupational PA, has been shown to reduce the risk of T2DM, which may partly be mediated by reduced adiposity [27, 28]. Several studies have demonstrated that PA improves insulin sensitivity, glycaemic control, lipid profile, and blood pressure [29–31], with benefits lasting from 2 to 72 h after any PA [32]. Furthermore, regular self-monitoring of blood glucose (SMBG) and medication-taking are frequently considered in the context of diabetes self-management education and support [33]. Diabetes self-management education aims to improve diabetes-related health literacy, self-efficacy, and self-management abilities in a variety of contexts and forms for patients with diverse backgrounds, experiences, and clinical information. To improve the effectiveness, accessibility, acceptability, and cost-effectiveness of diabetes education, a variety of new and innovative technologies need to be applied, and they are more effective when used together for better metabolic control and outcomes [34–36].

Mobile health (mHealth) is increasingly being implemented into health care practice, revealing special benefits in providing rapid, abundant, and tailored medical information to various groups of individuals, with lower health care costs and removed time and place restrictions [36–38]. A number of randomized controlled trials have shown the efficacy of applying mHealth technologies for lifestyle change and HbA1c improvement in T2DM [39, 40], such as the Norwegian Randomized Controlled Trial RENEWING HEALTH [41], MyPlan 2.0 intervention (a self-regulation–based electronic and mHealth project) in two randomized controlled trials [42], a digital medicine offering (DMO) in a cluster-randomized pilot trial [43], and a fully automated Web-based program in the ANODE study [44]. However, despite the availability of a wide range of diabetes-specific mHealth apps available, more detailed evidence regarding their clinical usefulness is still required [45].

Artificial intelligence, defined as “a field of science and engineering concerned with the computational understanding of what is commonly called intelligent behavior and with the creation of artifacts that exhibit such behavior” [46], is being developed and applied in a variety of healthcare fields, especially decision support and knowledge acquisition. There are diverse intelligent algorithms and techniques in AI, such as machine learning (ML), natural language processing (NLP), robotics, fuzzy logic (FL), expert systems (ES), knowledge base (KB), and a combination of two or more methods [46]. To tackle clinical difficulties in T2DM, a large amount of data collecting, analysis, and application of knowledge is required. Therefore, an increasing number of AI-based projects for T2DM diagnosis [47–50], clinical decision-making [51–53], and disease probability or outcome prediction [46, 54–57] have been developed. knowledge graph is a research field of AI that is graph that includes entities, properties, and relations between entities, which is usually stored in the form of inter-connecter triples [58]. KG-based technologies are being developed to extract structured knowledge from massive data, which is considered as a crucial component for the development of AI in conjunction with big data and deep learning [58], especially in the medical domain [59]. Potential applications of KG technology in T2DM include medical information retrieval, medical knowledge intelligent question and answering (QA), diagnosis, and treatment. Knowledge-based question answering (KBQA) is a type of QA processing that uses a knowledge database to provide fast and accurate answers to questions written in natural language expressions by users [60]. It has been applied in disease diagnosis and treatment recommendation [61–63]. However, KBQA in T2DM is a research area that has yet to be fully investigated. Chang, et al. developed DiaKG, the first high-quality Chinese dataset for the diabetes knowledge graph, with 22,050 entities and 6,890 relations about clinical research, drug usage, clinical cases, diagnosis, and treatment methods of T2DM [59]. Chen, et al. created a KBQA-based personalized food recommendation framework based on FoodKG and American Diabetes Association (ADA) lifestyle guidelines that outperformed non-personalized counterparts in terms of recommending more relevant and healthier recipes [64]. Due to a lack of high-quality T2DM annotated corpora and KG, few studies used KG as a T2DM intervention to assess its effectiveness on self-management and clinical outcomes.

In summary, given the great potential of patient-oriented KBQA technology for diabetes prevention and control in primary healthcare, the primary goal of this study is to develop a personalized, sustainable and cost-effective health education intervention program, AI-HEALS, to improve the outcome and self-management skills of people with T2DM.

The specific objectives are:1. Evaluate the impact of the AI-HEALS-based intervention program on blood glucose control of T2DM patients.2. Determine the efficacy of the AI-HEALS-based intervention program in improving self-management abilities among T2DM people:2.1 The effectiveness of a healthy diet;2.2 The effectiveness of moderate PA;2.3 The effectiveness of regular medication administration;2.4 The effectiveness of regular blood glucose monitoring.3. Compare the acceptability and cost-effectiveness of AI-HEALS-based intervention program in T2DM primary healthcare.

## Methods

### Study design

This study will use a nested mixed-method study with a quantitative survey and a qualitative interview to gain a better understanding of the effect and acceptability of the AI and mHealth-based intervention program for T2DM. The research will take place from August 2023 to June 2025. The quantitative survey will be conducted as a community-based cluster randomized controlled trial with two parallel groups to compare the effectiveness of the AI-HEALS-based education program on T2DM control and self-management behaviors (such as medication use, dietary and physical activity modification). The intervention will last three months. Questionnaires, physical examinations, and personal in-depth interviews (the qualitative study) will be conducted to participants at baseline, 1, 3, 6, 12, and 18 months to examine changes in self-management behaviors and blood glucose control. Cost-effectiveness analysis will be conducted at 12 and 18 months. The flow chart for the study shown in Figs. 1 and 2.

**Fig. 1 Fig1:**
[figure not shown]
Flow chart of patient recruitment and study implementation

**Fig. 2 Fig2:**
[figure not shown]
The schedule of enrolment, interventions, and assessments

### Study setting and randomization

The study will be conducted in 40-45 community health centers (CHCs) in Beijing, China, as the unit of randomization. The community health center contains 8-10 people with T2DM. A computer-generated list of random numbers will assign clusters (CHCs) in a 1:1 ratio to an intervention group and a control group. All subjects in each cluster will receive the same intervention (SDPC plus AI-HEALS) or control (SDPC). Blinding of the participants or researchers cannot be guaranteed considering the nature of the intervention. The proportion of sociodemographic characteristics (such as gender, age, and location) between two groups will be evaluated at baseline to verify that the data are balanced and comparable. Study designer will generate the allocation sequence, CHCs staff will enroll participants, and study designer will assign participants to interventions.

### Population

The study population for our program is residents aged 18–75 years with T2DM in CHCs. The inclusion criteria are as follows: meet T2DM diagnostic criteria [65] (fasting plasma glucose ≥ 7.0 mmol/L or 2 h plasma glucose ≥ 11.1 mmol/L or HbA1c ≥ 6.5%); permanent residence in Beijing; ability to use smartphones and the WeChat chatting app; have not taken any psychotropic drugs prior to enrolment; have not participated in other studies; agree and able to adhere to the study. A history of type 1 diabetes, gestational diabetes, or secondary diabetes; severe diabetes complications; having radiotherapy or chemotherapy within the last six months; severe intellectual disability, Alzheimer's disease, or other mental disorders are key exclusion criteria. We have not yet started recruiting study participants, and we expect to begin recruitment in July 2023. After completing the entire questionnaire, participants will receive a gift of about 20 CNY. Participants will be informed that their participation is voluntary and that they can always opt out and switch to the SDPC.

### Effect size

Based on our previous study, assuming an alpha risk of 0.05, a beta risk of 0.10, an intraclass correlation (ICC) of 0.002, a mean level of HbA1c in patients with type 2 diabetes of 7.13%, and a standard deviation (SD) of 1.60%, at least 2 clusters, and 166 subjects (138 total before considering a dropout rate of 20%) in each cluster are expected to be recruited according to the sample size formula for unmatched studies [66] to detect a decrease in HbA1c to 6.50% after the intervention. As a result, a total of 664 patients in 4 communities are required to be recruited for this program.

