### Statistical analysis

Data from the quantitative study will be recorded in the designed questionnaire and double-parallelly entered into Epidata 3.1 (Version 15.0.5, Odense, Denmark). Variables analysis will be based on the premise of intention to treat. Continuous variables will be presented as mean ± SD (M(P_25_, P_75_), if they are abnormal distribution), and be compared using Student's t test or one-way ANOVA (or non-parametric tests if necessary). Data distribution will be identified by a Kolmogorov–Smirnov test. Categorical data reported as n(percentage of sample) will be compared using χ2 tests. With regard to the cross-sectional analysis, linear regression, logistic regression and structural equation model (SEM) will be conducted to explore the influence factors of behaviors pattern and mHealth usage pattern evaluated by the group-based trajectory model (GBTM). For longitudinal data, a generalized linear mixed model (GLMM) will be used to identify the effectiveness of the AI and mHealth-based intervention in behavioral changes and diabetic control. Set an alpha risk of 0.05 for two-sided tests. Data will be analysed using IBM SPSS Statistics version 24.0 (SPSS Inc., an IBM Company, Chicago, Illinois, USA), Stata (version 14.0, Stata Corporation, College Station, TX) and M*plus* (version 7.4, Muthén & Muthén, Los Angeles, CA, USA).

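### The printed sample size (2 clusters per arm, 138 per cluster, 664 in 4 communities) does not follow from its own inputs; 138 matches a per-arm figure

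*Protocol article*

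**What the plan says.** The Effect size section of the protocol article sets out its error rates and clustering as "assuming an alpha risk of 0.05, a beta risk of 0.10, an intraclass correlation (ICC) of 0.002". The reference value is "a mean level of HbA1c in patients with type 2 diabetes of 7.13" percent, the SD is 1.60%, and the value to be detected after intervention is 6.50%. The section names a sample size formula for unmatched studies, by citation only. The result is "at least 2 clusters, and 166 subjects (138 total before considering a dropout rate of 20%) in each cluster are expected to be recruited", and then: "As a result, a total of 664 patients in 4 communities are required to be recruited for this program".

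The Statistical analysis section fixes the sidedness: "Set an alpha risk of 0.05 for two-sided tests".

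The Study setting and randomization section describes a different layout: 40-45 community health centres (CHCs) randomised 1:1, each with 8-10 people with type 2 diabetes.

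**The concern.** Inputs and result are both printed, so the result can be checked, and it fails the check. The number 138 lies very close to what an individually randomised trial would need in each arm, yet it is labelled as the number in each of two clusters per arm. This is the only justification of size and power in the article. If it is carried forward when the size is restated for the centres actually randomised, the trial will quote a power that no calculation supports. The point is distinct from the mismatch in the number of centres and from the way dropout is added, although one rewrite of the section can settle all three.

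**Working it through.** **Inputs.** From Effect size: alpha 0.05, power 0.90, ICC 0.002, SD 1.60, difference 7.13 − 6.50 = 0.63, dropout 20%. From Statistical analysis: two-sided tests. Clusters per arm: 664 / 166 = 4 communities, so 2 per arm under 1:1 allocation (inferred).

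**Step 1: size without clustering.**
n0 = (1.960 + 1.282)² × 2 × 1.60² / 0.63² = 10.507 × 5.12 / 0.3969 = 135.5, so 136 **per arm** (137 with a t correction).

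**Step 2: trying to reproduce 138 per cluster with c = 2 clusters per arm.**

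- Plain design effect: 2m = n0 × [1 + (m − 1) × 0.002], so m = 135.5 × 0.998 / (2 − 135.5 × 0.002) = 135.27 / 1.729 = 78.2, rounded up to **79**.
- Unmatched formula with one extra cluster per arm (assumed form), c = 1 + n0 × [1 + (m − 1) × 0.002] / m. At c = 2, m = 135.27 / (1 − 0.2711) = 185.6, rounded up to **186**. If the ICC is first converted to a between-cluster coefficient of variation using the mean of 7.13, m is about 180. At m = 138 the formula returns c = 2.25, which rounds up to 3 clusters per arm.
- One-sided alpha (111 per arm unclustered) and 80% power (102 per arm) do not explain 138 either.

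**Step 3: what does give about 138.**

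- n0 multiplied by the design effect at the CHC size in Study setting: 135.5 × (1 + 7 × 0.002) = 137.4 for 8 per centre, and 135.5 × (1 + 9 × 0.002) = 138.0 for 10. Both round up to **138 per arm**.
- The unmatched formula with 0.002 entered as a coefficient of variation gives 136.9, so 137 per cluster.

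The plan's later arithmetic is consistent with itself: 138 × 1.2 = 165.6, so 166, and 4 × 166 = 664.

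**Step 4: power of the printed layout (2 × 138 per arm).**
Design effect 1 + 137 × 0.002 = 1.274; effective size 276 / 1.274 = 216.6 per arm; standardised effect 0.63 / (1.60 × √(2 / 216.6)) = 4.098.

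| Method | 138 per cluster | 133 per cluster (166 less 20%) |
|---|---|---|
| Normal approximation | 98% | 98% |
| Unmatched formula, one extra cluster per arm (assumed form) | 83% | 81% |
| t test on cluster means, 2 df | 58% | 57% |

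Simulation of the 2 df test at 138 per cluster also gave 58%.

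**Step 5: power of the layout in Study setting.**
t test on cluster means with (clusters − 2) df and ICC 0.002. Forty-five centres cannot be split evenly, so 44 is used as the upper case.

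| CHCs per arm | Patients per CHC | All evaluable | After 20% loss |
|---|---|---|---|
| 20 | 8 | 92.6% | 86.3% |
| 20 | 10 | 96.7% | 92.6% |
| 22 | 8 | 94.8% | 89.4% |
| 22 | 10 | 97.9% | 94.8% |

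First row after loss: 6.4 evaluable per centre; design effect 1 + 5.4 × 0.002 = 1.0108; effective size 128 / 1.0108 = 126.6 per arm; standardised effect 3.133; 38 df.

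**The case against.** The strongest defence is that the underlying calculation may be sound and only its label wrong. As Step 3 shows, 138 is what the inputs give per arm for centres of 8-10, with the ICC used properly. With the plan's 20% addition this is 166 per arm and 332 in total; at 8 per centre that is 332 / 8 = 41.5 centres, inside the 40-45 range. This stands as the better-fitting explanation, and it weighs against a reading that a reader might adopt: that clustering was ignored, or that the ICC was entered as a coefficient of variation. The document does not show either. The coefficient-of-variation route gives 137 and leaves the 40-45 centres unexplained. But the defence does not rescue the text, because a per-arm figure printed as per cluster and then doubled to 664 in 4 communities is still an error.

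The second defence concerns power. A reader might take the 58% as proof that the trial is badly underpowered. The documents do not support that. The printed 276 per arm is about twice the unclustered need; the low figure comes from having only four clusters. The planned analysis is a generalized linear mixed model whose degrees-of-freedom method can properly be left to an analysis plan. The four-community layout is also not the one described for conduct. The 83% and the 186 rest on a formula whose source is not shown. All of this stands, and it limits the point to the stated justification.

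**Conclusion.** The point holds as a defect in the stated justification. From the printed inputs, 2 clusters per arm with 138 each is not the size for 90% power: the plain design effect gives 79 per cluster, and the assumed unmatched formula about 186. The figure appears to be a per-arm number printed as per cluster and then doubled, but how it was derived cannot be known from the document. None of the three methods tried gives 90% power for the printed layout (98%, 83%, 58%), and whether it is over- or under-sized depends on the analysis.

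The conclusion assumes two clusters per arm, inferred from 664 / 166, and 0.002 used as an ICC, as it is labelled. The conduct layout of 40-44 CHCs is adequately sized on the same inputs in most cases: 93% to 98% before dropout and 86% to 95% after. Only the cases with 8 enrolled per centre fall below 90% after loss.

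**What to change.** In Effect size, replace the two-cluster, 138/166-per-cluster and 664-in-4-communities result with one calculation for the CHCs that will be randomised, reconciled with Study setting and randomization. State the number of centres per arm and patients per centre, and label every figure as per centre, per arm or total. Use 0.002 as an ICC (between-cluster variance 0.002 × 1.60² = 0.00512), write out the formula, and use a small-sample reference based on the number of clusters. Quote the power that remains after 20% dropout in place of the present 90%.

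The cost is one recalculation and revised wording, with no extra enrolment. The quoted power may fall slightly below 90% at the low end (about 86% with 40 centres of 8). The Population section says recruitment had not begun when the article was written, so the change could be made before enrolment.

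### The 20% dropout allowance multiplies by 1.2 instead of dividing by 0.8, so 166 per cluster (664 in total) does not retain the 138 per cluster the plan requires

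*Protocol article*

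**What the plan says.** The Effect size section of the protocol article sets a 5% type I error and 90% power. It takes 7.13% as the reference HbA1c, 1.60% as the SD and 0.002 as the ICC. The target is stated as "to detect a decrease in HbA1c to 6.50% after the intervention". The number it then asks for, with a minimum of two clusters, is "166 subjects (138 total before considering a dropout rate of 20%) in each cluster". The section closes by concluding that "a total of 664 patients in 4 communities are required".

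The Statistical analysis section adds "Set an alpha risk of 0.05 for two-sided tests". The Outcomes section treats drop-out in the ordinary sense of participants leaving the trial. Nowhere does the article give the 20% another meaning or state another inflation rule.

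**The concern.** As worded, 138 is the number needed per cluster before attrition, and 166 is that number adjusted for 20% attrition. The two do not fit: a fifth of 166 is 33.2, and removing it leaves fewer than 138. The pattern suggests that 20% of the required number was added, when the required number should have been divided by the expected retention.

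At stake is the headline recruitment figure, which the article presents as a requirement. Follow-up runs to 18 months, so the allowance should deliver what it claims. The same section will also have to be revisited because its four communities do not match the 40–45 health centres in Study setting and randomization. If the 1.2 factor were reused there, it would again understate recruitment or overstate the analysable number.

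**Working it through.** **Inputs (Effect size section).** Required per cluster before dropout n = 138; dropout d = 0.20; stated recruitment 166 per cluster and 664 in 4 communities.

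**Reproducing the stated figures.**
- n × (1 + d) = 138 × 1.2 = 165.6, rounded to 166.
- 4 × 166 = 664.

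Both match exactly, so this is the rule that was used.

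**Checking them against the stated dropout.**
- 166 × 0.80 = 132.8 per cluster, against 138 required.
- 664 × 0.80 = 531.2 in total, against 4 × 138 = 552.
- Dropout that 166 can absorb: 1 − 138/166 = 16.9%.

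**The inflation that retains 138.**
- n / (1 − d) = 138 / 0.80 = 172.5, rounded up to 173 per cluster.
- Total: 4 × 173 = 692, or 552 / 0.80 = 690 if rounded only at the end.
- Shortfall: 173 − 166 = 7 per cluster; 690 − 664 = 26 to 692 − 664 = 28 overall. 28/664 = 4.2% of the stated total.

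**Effect on power in the four-cluster layout.** Two clusters per arm, difference 7.13 − 6.50 = 0.63, SD 1.60, ICC 0.002, two-sided 5%. The design effect is 1 + (m − 1) × 0.002, which is 1.274 for m = 138 and 1.264 for m = 132.8. With two clusters per arm the standard error of the difference is √(1.60² × design effect / m), which is 0.1537 and 0.1561. The ratio of 0.63 to the standard error is 4.10 and 4.04.

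| Method | m = 138 | m = 132.8 | Loss (points) |
|---|---|---|---|
| Normal approximation with design effect | 98.4% | 98.1% | 0.3 |
| Cluster formula with one extra cluster per arm | 82.6% | 81.4% | 1.1 |
| Cluster-level t-test, 2 degrees of freedom | 58.1% | 57.1% | 1.0 |

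The levels differ greatly because four clusters leave almost no degrees of freedom. The loss due to the dropout step is about one point or less on each method.

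**Does the error depend on reading 138 as a per-cluster number?** Without clustering, the two-sample formula gives 2 × (1.960 + 1.282)² × 1.60² / 0.63² = 135.5 per arm. Multiplied by a design effect of 1.014 to 1.018 (clusters of 8–10), this is 137.4 to 138.0 per arm. So 138 reproduces as a per-arm number. As a per-cluster number with two clusters per arm it does not: the design-effect formula gives about 78, and the formula with the extra cluster gives about 186 (two-sided) or 142 (one-sided). Read per arm, the same slip gives 166 instead of 173 per arm, or 332 instead of 346 in total. The factor is wrong on either reading.

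**The case against.** The arithmetic is not open to dispute; the objections concern its weight and its remedy.

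- **The effect is minor.** A 4% shortfall is small beside the uncertainty in the assumed SD, ICC and dropout rate, and 166 still absorbs 16.9% dropout. This stands. No conclusion of the trial is likely to turn on it. It makes the point a cheap correction, but it does not make the figure right.
- **The base of 138 per cluster does not itself reproduce.** This also stands. The 173 and 692 are what the plan's own 138 implies, and should not be taken as a verified sample size.
- **The larger fault is the conflict with the design.** Study setting and randomization describes 40–45 centres with 8–10 people each, about 320 to 450 in total, against 664 in four communities. That is a separate and bigger problem, and resolving it will probably replace all three numbers. Until then the stated figures are in force, and any new calculation needs the correct dropout rule.
- **Completers are not the same as analysable participants.** With intention to treat, a mixed model and repeated HbA1c measurements, someone who leaves after month 3 can still contribute. So 531 is strictly a count of completers. The plan's own inflation uses the same completer logic, so this does not rescue the step.

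**Conclusion.** The concern holds. On the plan's own 138 and 20%, the recruitment target should be 173 per cluster and 690–692 in total; the stated 166 and 664 are short by 7 and by 26–28 (about 4%). The power lost is 0.3 to 1.1 percentage points in the four-cluster layout.

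This rests on two assumptions: that the 20% is a proportion of those recruited, for which the article offers no alternative, and that 138 is per cluster as written. If 138 was meant per arm, the totals become 346 against 332 and the error is the same. It is a certain error in the primary sample-size statement, small in consequence, and worth correcting.

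**What to change.** If the present calculation stays, state the inflation as n/(1 − 0.20) and change 166 to 173 per cluster and 664 to 692. The cost is one corrected factor and 26–28 more patients in the stated total. Before doing so, confirm whether 138 is per cluster or per arm.

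If the calculation is redone for the 40–45 centres, take the analysed size as 0.8 × the recruited size. Assuming that 8–10 is the number recruited per centre, this is 6.4–8 analysed per centre. The table uses the plan's difference, SD, ICC and two-sided 5% with the normal approximation:

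| Centres × recruited per centre | Recruited | Analysed | Approximate power |
|---|---|---|---|
| 40 × 8 | 320 | 256 | 88% |
| 45 × 8 | 360 | 288 | 91% |
| 40 × 10 | 400 | 320 | 94% |
| 45 × 10 | 450 | 360 | 96% |

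The intended 90% ("a beta risk of 0.10") is met without added patients except at the smallest combination, where 256 analysed falls below 2 × 138 = 276. For most of the range the change therefore costs only a restated analysable number and power. At the low end the plan should commit to more centres or more people per centre. The article says recruitment had not begun, so at that stage the correction could still be made before enrolment.

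### The required size (664 patients in 4 communities) and the randomised design (40-45 health centres of 8-10 patients) cannot both hold, so the 90% power is not tied to one consistent design

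*Protocol article*

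**What the plan says.** The Effect size section gives the only sample-size justification. Its inputs are "assuming an alpha risk of 0.05, a beta risk of 0.10", "an intraclass correlation (ICC) of 0.002", a mean HbA1c of 7.13% to be lowered to 6.50%, and an SD of 1.60%. It arrives at a minimum of 2 clusters (per arm, as the total of 4 implies) with 138 subjects per cluster, raised to 166 for 20% dropout. It ends: "a total of 664 patients in 4 communities are required to be recruited for this program". The Statistical analysis section makes the tests two-sided: "Set an alpha risk of 0.05 for two-sided tests".

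The Study setting and randomization section describes something else. The trial takes place in "40-45 community health centers (CHCs) in Beijing, China, as the unit of randomization", allocated 1:1, and "The community health center contains 8-10 people with T2DM". The Methods part of the abstract agrees on the number of centres: patients "will be recruited from 40-45 community health centers in Beijing, China".

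**The concern.** The same article gives two numbers of clusters (4 and 40-45), two cluster sizes (166 and 8-10) and, by multiplication, two totals (664 and 320-450). HbA1c is the primary outcome and this is its only size calculation.

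Centres therefore have no single recruitment target, and a later reader could not tell whether a total of, say, 400 is complete or a shortfall. Power in a cluster trial also depends on how many clusters there are and how large they are, so "a beta risk of 0.10" means little until those are fixed. The Population section says recruitment had not begun, so the correction was still cheap.

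**Working it through.** **1. The two designs side by side**

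| | Effect size section | Randomisation section and abstract |
|---|---|---|
| Clusters | 4 | 40-45 |
| Patients per cluster | 166 | 8-10 |
| Total | 4 × 166 = 664 | 40 × 8 = 320 to 45 × 10 = 450 |

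The gap is 664 − 450 = 214 to 664 − 320 = 344 patients, or 32-52% of 664. Reaching 664 needs 664/45 = 14.8 to 664/40 = 16.6 patients per CHC, or 664/10 = 66 to 664/8 = 83 CHCs.

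**2. Reproducing 138, 166 and 664**

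Inputs: difference d = 7.13 − 6.50 = 0.63; SD 1.60; two-sided alpha 0.05; power 0.90; f = (1.960 + 1.282)² = 10.507. Without clustering, n per arm = 2 × 10.507 × 1.60²/0.63² = 135.5.

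*Route A: two large clusters per arm.* The standard formula for unmatched cluster trials is c = 1 + f[2·SD²/m + k²(μ₀² + μ₁²)]/d². With m = 138 and 0.002 entered as the between-cluster coefficient of variation k, c = 1.992, so 2 clusters per arm suffice (the smallest such m is 137). With 0.002 used as an ICC, as the protocol labels it, c = 2.25 at m = 138, and m = 186 would be needed for c = 2.

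*Route B: small clusters, 0.002 as an ICC.* Multiply 135.5 by the design effect 1 + (m − 1) × 0.002. For m = 8, 9 and 10 this gives 137.4, 137.7 and 137.99, all rounding up to 138, but now per arm.

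In both routes 138 × 1.2 = 165.6, i.e. 166. Route A then gives 4 × 166 = 664; Route B gives 2 × 166 = 332. The text does not show which was used. (Allowing for dropout by dividing gives 138/0.8 = 172.5, i.e. 173.)

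**3. Power of the 40-45 CHC design on the protocol's inputs**

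The variance of a cluster mean is SD²[ICC + (1 − ICC)/m], where m is the number analysed after 20% dropout. The standard error is √[variance × (1/k₁ + 1/k₂)]. Power is from the noncentral t with k₁ + k₂ − 2 df.

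Example, 40 × 8: m = 6.4; variance = 2.56 × (0.002 + 0.998/6.4) = 0.4043; SE = √(0.4043 × 2/20) = 0.2011; noncentrality 0.63/0.2011 = 3.13; 38 df, critical t 2.024; power 86.3%.

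| CHCs × recruited (arms) | ICC 0.002 | ICC 0.02 (assumed) | ICC 0.05 (assumed) |
|---|---|---|---|
| 40 × 8 (20/20) | 86.3% | 83.1% | 77.8% |
| 45 × 8 (22/23) | 90.1% | 87.3% | 82.6% |
| 40 × 10 (20/20) | 92.6% | 89.5% | 84.0% |
| 45 × 10 (22/23) | 95.2% | 92.8% | 88.1% |

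Only the 0.002 column uses an ICC from the protocol. With 40 CHCs, 9.1 recruited per CHC (7.28 analysed, about 365 in total) gives 90.2% at ICC 0.002.

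**4. Power of a literal 2-against-2 trial**

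m = 138; variance = 2.56 × (0.002 + 0.998/138) = 0.0236; SE = √(0.0236 × 2/2) = 0.1537; noncentrality 4.10; 2 df, critical t 4.303; power 58.1%. The normal approximation, which ignores the 2 df, gives 98.4%.

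**The case against.** The mismatch itself is hard to dispute. The case against making more of it has four parts.

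*The 90% may belong to the CHC design after all.* Route B uses the ICC as labelled and the small cluster sizes, and it also gives 138 and 166, per arm. The total of 332 equals 41.5 CHCs of 8, inside 40-45. On that reading the printed sentence is a garbled per-arm result and 664 a spurious doubling. This is inference, but so is Route A. A reader might conclude that the calculation was done for a different trial; the documents do not prove it. What stands is that the printed text ties the 90% to no consistent design.

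*A reader might infer that the trial will miss its required number and be underpowered.* The first part depends on taking 8-10 as enrolment per CHC, whereas the sentence only says what a centre contains, and no section states a total of 320-450. The second part is not supported: at the protocol's ICC, power runs from 86% to 95%, on both sides of 90%. The lower figures need ICCs that the protocol does not give.

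*A reader might infer that a 4-community trial could hardly ever reach significance.* That holds only for an exact re-randomisation test of 2 against 2, where the smallest two-sided p is 2/6 = 0.33. The protocol plans a generalized linear mixed model, not that test. The 58% is likewise for a cluster-level t test chosen here as a benchmark, and two sections say that 40-45 CHCs will be used. The point matters only if the Effect size section were followed to the letter.

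*Striking out 664 would prejudge which section governs.* This is fair. The section calls that number required, and a larger total has value: 664 spread over 40-45 CHCs, with the same method, 20% dropout and an assumed ICC of 0.05, gives about 94-95% power, against 78-88% for 320-450. The sponsor must reconcile the sections first.

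None of this removes the contradiction. Reading communities as a level above CHCs does not help either: 166 is stated per cluster, the randomisation section equates clusters with CHCs, and 664 over 40-45 CHCs is still 15-17 each.

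**Conclusion.** The point holds as an unreconciled contradiction in the number of clusters (tenfold), the cluster size (166 against 8-10) and the total (664 against 320-450, a gap of 214-344). The stated power cannot be attached to the trial until it is resolved.

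The 40-45 CHC design is not shown to be seriously underpowered: 86% at 40 × 8 to 95% at 45 × 10. This rests on a difference of 0.63, SD 1.60, ICC 0.002, 20% dropout, equal cluster sizes, 8-10 being enrolment per CHC, and a cluster-level t test. A literal 4-cluster trial would be the weaker design, at about 58% on the same inputs. It should be corrected because the trial's only size statement cannot be used as printed, not because of low power.

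**What to change.** Reconcile the abstract, the Study setting and randomization section and the Effect size section to one number of CHCs, one recruited number per CHC and one total. Then recompute and restate the sample size and power for that design: 20-23 CHCs per arm if 40-45 stands, a cluster-adjusted variance, degrees of freedom equal to clusters minus 2, and dropout applied. Say whether 0.002 is an ICC or a coefficient of variation.

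If 40-45 CHCs of 8-10 is the design, replace the 4-community statement with 320-450 patients and 86-95% power at ICC 0.002, noting that 40 CHCs need about 9.1 recruited each for 90%. If 664 is the requirement, change the number per CHC or the number of CHCs to match. In either case add a short ICC sensitivity range; for 320-450 patients an assumed ICC of 0.05 gives 78-88%.

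For the 320-450 design the cost is one rewritten paragraph and a stated power slightly below 90% at the low end, with no patients beyond the 8-10 per CHC already described. Keeping 664 would mean more patients per CHC or more CHCs.
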